## Abstract

**Background:**

Rehabilitation after spinal cord injury (SCI) has traditionally involved teaching compensatory strategies for identified impairments and deficits in order to improve functional independence. There is some evidence that regular and intensive activity-based therapies, directed at activation of the paralyzed extremities, promotes neurological improvement. The aim of this study is to compare the effects of a 12-week intensive activity-based therapy program for the whole body with a program of upper body exercise.

**Methods/Design:**

A multicenter, parallel group, assessor-blinded randomized controlled trial will be conducted. One hundred eighty-eight participants with spinal cord injury, who have completed their primary rehabilitation at least 6 months prior, will be recruited from five SCI units in Australia and New Zealand. Participants will be randomized to an experimental or control group. Experimental participants will receive a 12-week program of intensive exercise for the whole body, including locomotor training, trunk exercises and functional electrical stimulation-assisted cycling. Control participants will receive a 12-week intensive upper body exercise program. The primary outcome is the American Spinal Injuries Association (ASIA) Motor Score. Secondary outcomes include measurements of sensation, function, pain, psychological measures, quality of life and cost effectiveness. All outcomes will be measured at baseline, 12 weeks, 6 months and 12 months by blinded assessors. Recruitment commenced in January 2011.

**Discussion:**

The results of this trial will determine the effectiveness of a 12-week program of intensive exercise for the whole body in improving neurological recovery after spinal cord injury.

**Trial registration:**

NCT01236976 (10 November 2010), ACTRN12610000498099 (17 June 2010).

## Background

Rehabilitation after spinal cord injury (SCI) has been traditionally based on expectations regarding functional outcomes predicted by the initial level of injury and severity of impairment [1]. It has relied substantially on compensatory strategies for identified impairments and deficits that were considered irremediable, because significant recovery of motor function was not expected beyond that defined by clinical assessments [2]. Thus, in patients with clinically complete injuries, therapy has been primarily directed at activities to improve functional independence, e.g., teaching new strategies to move in bed and transfer into and out of a wheelchair, and provision of assistive devices [2]. This strategy is reliant on strengthening muscles above the spinal lesion level and using leverage, momentum and substitution to move weak or paralyzed parts of the body. While this approach results in improvements of independent function, it does not promote recovery of motor control in the paralyzed limbs [3]. In addition, because of funding limitations available for in-patient rehabilitation, therapists have had to focus on targeting immediate needs for independence in preparation for discharge [2].

Regular physical activity through upper body training is effective in improving cardiorespiratory fitness, muscle strength [4,5] and psychological well-being in the SCI population [6]. However, there is new evidence that regular and intensive *activity-based therapies*, directed at activation of the paralyzed extremities, promotes neurological improvement [2,7-9]. These therapies include partial body-weight-supported locomotor training (LT), functional electrical stimulation (FES)-assisted leg exercise, and exercises to improve control of trunk and lower limb musculature. To date, the interventions have been investigated as single entities; however, Harness et al. [9] conducted a study involving a combination of these interventions. They reported that people with spinal cord injury receiving intensive exercises focused on attempting to regain voluntary motor function below the level of injury showed improvement in motor function, whereas those undertaking a self-directed exercise program did not show any improvements. However, the study had a number of limitations, including a non-randomized design and significant difference between groups in time post-injury.

While most research attention has focused on the benefits of these types of therapy for people with incomplete lesions [10,11], those with complete lesions may also benefit since it is recognized that many people with complete injuries are electrophysiologically incomplete (discomplete) [12,13]. In these cases, patients who are clinically paralyzed show sub-clinical evidence of translesional motor connections [14]. These subclinical responses can take various forms, for example, repeatable responses to reinforcement maneuvers or to strong vibration [15] or the ability to volitionally suppress responses evoked by plantar surface stimulation [16,17]. The objective of this project, therefore, is to determine the effectiveness of an intensive activity-based therapy program for patients with complete and incomplete spinal cord lesions. This will involve LT, FES-assisted leg cycling as well as trunk, upper limb and lower extremity exercises. In the case of complete spinal cord injury, LT will be used to explore the potential for stimulating neurological improvement rather than as a means of attaining functional ambulation [18]. The control intervention will comprise solely upper body exercises.

## Methods

The trial has been registered on ClinicalTrials.gov (NCT01236976) and the Australian and New Zealand Clinical Trials Registry (ACTRN12610000498099).

### Design

A multicenter, assessor-blinded, randomized controlled trial will be conducted. Experimental group participants will undertake an intensive 12-week program of whole body exercise, including their paralyzed lower limbs, while control group participants will undertake an upper body strength and aerobic fitness training program over the same period. The trial will be conducted in six spinal units in Australia and New Zealand. Ethical approval has been obtained from the Human Research Ethics Committee at each site (see Additional files 1 and 2) and at the University of Melbourne (HREC 1034730). Participants will be provided with information sheets, and written informed consent will be obtained prior to recruitment and baseline assessment.

### Participants

One hundred eighty-eight participants who are at least 6 months post-spinal cord injury will be recruited through referral by medical practitioners or therapists from one of the six participating spinal cord injury units involved or through advertisements placed in newsletters of Spinal Cord Injuries Australia, Independence Australia, on the SCIPA website (http://www.scipa.unimelb.edu.au) and collaborator websites. Those interested in participating will undergo an initial telephone screening survey comprising questions relating to their medical history and the protocol inclusion and exclusion criteria.

### Inclusion criteria

Participants will be included if they:

1. Have sustained a traumatic spinal cord injury a minimum of 6 months prior to consent and have completed their primary rehabilitation

2. Are 18 years or older and able to give informed consent

3. Have a complete or incomplete spinal cord injury between C6 and T12 (as per the International Standards for Neurological Classification of SCI [19]

4. Are able and willing to attend an exercise program three times per week for 12 weeks

5. Are considered by their medical consultant to be fit to undertake the exercise program (documented approval by medical consultant required).

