### Randomization

Participants will be randomly assigned to either the experimental or control group with a 1:1 allocation as per a computer-generated randomization schedule stratified by site and injury status [American Spinal Injuries Association Impairment Scale (AIS) A/B or AIS C/D]. The randomization schedule will be under the control of a central randomization unit, independent of the trial, located at Neuroscience Trials Australia. A participant will be considered to have entered the trial once his/her randomization is revealed.

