### Primary outcome

#### The primary outcome measure is the American Spinal Injuries Association (ASIA) motor score at 12 weeks

The ASIA Motor Score is derived from part of the assessment for the International Standards for Neurological Classification of Spinal Cord Injury [19]. It involves testing the strength of ten key muscles on each side of the body in the supine position (e.g., elbow flexors, wrist extensors, hip flexors, quadriceps, dorsiflexors) on a scale of 0 = no contraction to 5 = normal resistance through full range of motion. Scores are summed to give a total possible score of 50 for the upper extremities and 50 for the lower extremities.

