#### Statistical analysis

The primary and secondary endpoints analyses will be conducted by an independent statistician on an intention-to treat basis and using the full data set comprising all randomized participants. In addition, a *per protocol* analysis of the primary outcome will be reported. The data set for this analysis will comprise participants who adhered to all aspects of the protocol and received at least 80% of the training sessions. Multiple imputation of missing values will be conducted. All variables will be expressed as means, SD or median (IQR), unless otherwise indicated. Baseline comparisons between the two arms of the study will be made using means or medians and proportions with 95% confidence intervals as appropriate.

All endpoints and analyses have been prospectively categorized as either primary or secondary. Differences in both primary and secondary endpoints between the two arms of the study will be tested independently at the 0.05 level of significance, using a one-way ANCOVA model that will include the baseline value of the given outcome in question as a covariate. No formal adjustments will be undertaken to constrain the overall type I error associated with the secondary analyses. Their purpose is to supplement evidence from the confirmatory primary analysis to help more fully characterize the treatment effect. Results from the secondary analyses will be interpreted in this context.

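### Time since injury is neither stratified on nor adjusted for, which costs a little precision but causes no bias; separately, the six-month entry clock is stated two ways

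*Protocol article*

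**What the plan says.** **Entry.** The abstract (Methods/Design) describes participants "who have completed their primary rehabilitation at least 6 months prior". The Participants section says that "participants who are at least 6 months post-spinal cord injury will be recruited". Criterion 1 under Inclusion criteria asks that they "Have sustained a traumatic spinal cord injury a minimum of 6 months prior to consent and have completed their primary rehabilitation". None of these sets an upper limit on time since injury.

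**Allocation.** Under Randomization, participants are "randomly assigned to either the experimental or control group with a 1:1 allocation", following a "computer-generated randomization schedule stratified by site and injury status". Injury status there means AIS A/B versus C/D. Time since injury is not a factor.

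**Analysis.** The primary endpoint is the ASIA motor score at 12 weeks. The Statistical analysis section tests all endpoints "using a one-way ANCOVA model that will include the baseline value of the given outcome in question as a covariate". No other covariate is named.

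**The pilot study.** The Background gives its limitations as "including a non-randomized design and significant difference between groups in time post-injury".

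**The concern.** By listing the pilot's difference in time post-injury as a limitation, the protocol treats that variable as relevant to motor change. With no upper limit, the trial can enrol people six months after injury alongside people many years after it. A baseline motor score does not fully separate the two: a recent and a long-standing participant may start from the same score and have different expected courses over 12 weeks. If time since injury predicts the 12-week score beyond baseline, leaving it out of the model puts that variation into the residual and leaves any chance difference between arms unadjusted.

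The entry clock raises a different issue. The two statements of the six-month rule describe different populations, and they differ at the early end, where any natural recovery would be expected to matter most. A conclusion about people with established injury needs one definition.

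**Working it through.** **1. Scale, from the plan's own figures.** The Sample size section gives a difference of 4.0, f = 0.22, 150 evaluable participants (75 per arm), two-sided 0.05 and power 0.8.

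- Noncentrality = f² × N = 0.0484 × 150 = 7.26, on 1 and 147 degrees of freedom. Power is 0.763, not 0.80; the printed f needs 165 participants for 80%. The stated 150 fits f of about 0.23. The dropout step does reproduce: 150/0.8 = 187.5, rounded up to 188. The power shortfall is a separate matter and is used here only to set the scale.
- For two equal arms f = difference/(2 × residual SD), so the residual SD = 4.0/0.44 = 9.09 and the residual variance = 82.6.
- Standard error of the treatment difference = 9.09 × √(2/75) = 1.48 points.

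**2. Is the comparison biased?** In 20,000 simulated 1:1 trials of 150 participants with no true effect, 20% recently injured (assumed), an extra 5 points in that group (assumed) and no adjustment, the rejection rate was 0.0496 and the mean estimate -0.01. The simulation error of that mean is about 1.48/√20,000 = 0.01. There is no bias and no inflation of type I error.

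**3. Chance imbalance.** The article gives neither the spread of time since injury nor a spontaneous recovery rate. Assume that 30% are early-phase and gain an extra d = 1 to 4 points over 12 weeks.

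- SD of the between-arm difference in early share = √(0.3 × 0.7 × 2/75) = 0.075.
- A 2-SD imbalance is 0.15. It shifts the estimate by 0.15 × 1 = 0.15 to 0.15 × 4 = 0.60 points.
- Against the planned 4.0 this is 4% to 15%. Against the standard error of 1.48 it is 0.10 to 0.41 standard errors.

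Wider assumptions (10-50% early-phase, 95% limits of imbalance) give the following:

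| Extra gain in early phase | Shift in the estimate |
|---|---|
| 2 points | 0.2-0.3 |
| 5 points | 0.5-0.8 |
| 10 points | 1.0-1.6 |

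**4. Precision.** Variance due to phase = 0.3 × 0.7 × d² = 0.21 to 3.36. Divided by 82.6, this is 0.3% to 4% of the residual variance. It is an upper figure for these inputs, because baseline score and AIS group may already carry part of it. Power at N = 150 and f = 0.22, with time since injury as a second covariate:

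| Residual variance explained | Power | N for 80% |
|---|---|---|
| 0% | 76.3% | 165 |
| 2% | 77.2% | 161 |
| 5% | 78.4% | 157 |
| 10% | 80.6% | 148 |
| 20% | 84.9% | 132 |

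The assumed 0.3-4% lies in the first three rows, so the gain is about two percentage points of power at most. A covariate that explains nothing leaves power at 76.3%.

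**5. The entry clock.** Take a person injured 7 months ago who finished primary rehabilitation 1 month ago. Criterion 1 and the Participants section admit that person; the abstract does not. The gap between the rules is the time from injury to completion of rehabilitation. If that is 3 to 6 months (assumption), the earliest entry is 6 months after injury under criterion 1 and 9 to 12 months under the abstract.

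**The case against.** A reader might infer that spontaneous recovery enters the primary comparison uncontrolled. The documents do not support that. Allocation is concurrent, 1:1 and held by an independent central unit, and the control arm trains over the same period, so natural recovery falls equally on both arms in expectation. Chance imbalance is already reflected in the standard error and p-value. The pilot's imbalance arose in a non-randomized study, and randomization is the main answer to it; criticising that study does not oblige this trial to adjust. All of this stands, and it limits the point to efficiency.

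It can also be said that the sizes rest on assumed inputs. The only change without activity-based therapy that the article reports is the pilot control group's 0.1 points (SD 0.5), which gives no support for a gain of 1 to 4. That is fair, although the article does not say how long after injury those controls were, so it does not settle the matter. A single-covariate ANCOVA is valid, and having no upper limit on time since injury is a legitimate choice of population.

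Finally, an unseen analysis plan may add covariates. It may, but the article does not leave the model open: it names one covariate, and adding another would be a change to what is stated.

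On the entry clock, the two body sections agree and only the abstract differs, so the contradiction is small. It remains a contradiction between two fully printed eligibility statements.

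**Conclusion.** The point holds as a free improvement in efficiency plus a small inconsistency to correct. Omitting time since injury does not bias the treatment effect or disturb the type I error. Under the assumption of 30% early-phase participants with an extra 1 to 4 points, the cost is 0.3-4% of residual variance, and a 2-SD imbalance would move the estimate by 0.15-0.6 points, with either arm equally likely to benefit. Larger effects need larger assumed recovery, for which the article gives no evidence. The adjustment is still worth making because the variable is already held and, at the printed f, the design has no precision to spare.

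A reader might also infer that the two entry clocks undermine the between-arm comparison. They do not: either rule applies equally to both arms. What they affect is the description of the population to which the result applies.

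**What to change.** Prespecify time since injury at randomization as an additional covariate in the primary ANCOVA and in the 6- and 12-month motor-score analyses. Choose one functional form in advance, such as log months, and record the choice before any unblinded efficacy data are seen. The Monitoring section plans no interim efficacy analysis, so there is room to do this. The injury date is already needed to verify criterion 1; the cost is one degree of freedom and no new data. Stratification need not change, which matters because recruitment has started.

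Reconcile the abstract with the Participants section and criterion 1 so that a single six-month clock is stated, and describe the trial population in the conclusion by that clock. This is a one-line correction.

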### Exclusion criteria

Participants will not be included if they:

1. Have brachial plexus, cauda equina or peripheral nerve injury

2. Have had recent major trauma or surgery within the last 6 months

3. Have an existing stage 3 or 4 pressure ulcer according to the National Pressure Ulcer Advisory Panel classification [20]

4. Are post-menopausal at the time of injury (females)

5. Have a BMI at injury falling below the lower threshold of the healthy adult reference range

6. Have endocrinopathy or metabolic disorders of the bone, such as Paget’s disease, lytic or renal bone disease, and senile osteoporosis

7. Have a medical history of exposure to medication(s) known to affect mineral or bone metabolism

8. Have chronic systemic diseases, e.g., hepatitis C or HIV-AIDS

9. Have significant impairment or disability, including physical, neurological or psychological impairments, additional to the spinal cord injury

10. Have a history of long bone fracture or family history of fragility fracture

11. Have medical fragility, e.g., a BMI falling below the lower threshold of the healthy adult reference range, or history of recurrent hospital readmissions

12. Have extensive fixed contractures in the upper or lower limbs

13. Have severe spasticity

14. Have uncontrolled neuropathic pain

15. Are likely to experience clinically significant autonomic dysreflexia and/or orthostatic hypotension in response to electrical stimulation or prolonged upright postures

16. Are unable to attend the 6- and 120 month follow-up assessments at their treating spinal unit

17. Have any contraindications to FES such as a cardiac pacemaker, epilepsy, lower limb fracture or pregnancy

18. Have intracranial metal implants

19. Have any other serious medical condition including malignancies, psychiatric, behavioral or drug-dependency problems, which are likely to influence the participant’s ability to cooperate or in the opinion of the study investigator would prevent adherence to the protocol

20. Are participating in any other therapy (including alternative therapies) or taking medications (including herbal preparations) that are not considered to be standard care as per the protocol.

### Randomization

Participants will be randomly assigned to either the experimental or control group with a 1:1 allocation as per a computer-generated randomization schedule stratified by site and injury status [American Spinal Injuries Association Impairment Scale (AIS) A/B or AIS C/D]. The randomization schedule will be under the control of a central randomization unit, independent of the trial, located at Neuroscience Trials Australia. A participant will be considered to have entered the trial once his/her randomization is revealed.

### Intervention

All participants will attend the assigned exercise program for 36 sessions over 12 weeks, with an intended frequency of thrice weekly.

#### Experimental group

Participants in the experimental group will receive a triad of interventions comprising locomotor training, FES-assisted cycling as well as trunk and upper and lower extremity exercises. These interventions will be provided at the participating spinal units.

*Locomotor training* will be provided using a Therastride system (Innoventor, Inc., St Louis, MO, USA). Participants will be assisted to stand on the treadmill in an upright position and suspended in a harness by an overhead pulley at the maximum load necessary to avoid the knees collapsing into flexion. A therapist/assistant will be positioned behind the participant to stabilize the pelvis and trunk, as well as to assist weight shifting and hip rotation during the step cycle. This person will ensure that the trunk and pelvis are not flexed or hyperextended during stepping. Two therapists/assistants will be seated in front and to the side of the participant to provide manual assistance for the lower limbs to facilitate knee extension during stance and knee flexion and toe clearance during swing, maintaining appropriate alignment of the limbs. Manual assistance will be used as needed. Another therapist/assistant will control the treadmill. During the session, the treadmill speed will be adjusted to promote the best stepping pattern at the given body weight load. Speed will be progressively increased as appropriate to a normal walking speed range (0.89-1.34 m•s^-1^). Over the course of the study, the amount of body weight support can be reduced gradually as the participants improve their ability to bear weight on the lower limbs [21].

*FES-assisted cycling* will be provided using a RT300 cycle (Restorative Therapies, Baltimore, MD, USA). Surface electrodes will be applied over the belly of the quadriceps, gluteal and hamstrings muscles according to a standardized protocol. The pedal cadence will be set to 15–50 rev•min^-1^. Stimulation intensity will be gradually increased to a maximum of 140 mA with a pulse width of 0.3 ms at a frequency of 35 Hz [22,23]. Participants will exercise at the maximal power output possible at their level of recovery. They will undertake 30 min of cycling, initially in intermittent periods of exercise with rest breaks, but progressing to longer continuous exercise as deemed appropriate by supervising therapist/assistant. The frequency, power output, interval times and total training duration will be recorded at each training session.

*Trunk and upper and lower limb exercises* will comprise assisted and/or resisted movements aimed at facilitating and strengthening voluntary muscle activity and improving movement quality. These may be provided in lying (e.g., supine, prone, semi-recumbent) and in weight-bearing postures (e.g., kneeling, standing). Task-specific practice of functional tasks, involving moving the upper body over and outside the base of support, will also be undertaken. Participants may also be given exercises in motor imagery, i.e., imagining movements of their body [24]. Project staff will use their clinical judgment to select exercises suitable for each participant and to progress them as appropriate. All exercises selected will be documented in the participant source notes.

